#### Sample size

Sample size calculations are performed using G*Power 3.1.9.7 software [23]. For the primary analysis examining the time × treatment interaction effect, an F-test for ANOVA: repeated measures, within-between interaction is selected. Parameters are set as follows: effect size f = 0.25 (converted from Cohen’s d = 0.5), α error probability = 0.05, power (1-β error probability) = 0.95, number of groups = 2, number of measurements = 3 (baseline, midpoint, post-intervention), correlation among repeated measures = 0.5 (estimated from previous resistance training studies in cancer populations), and nonsphericity correction ε = 1. The moderate effect size (Cohen’s d = 0.5) is selected based on previous research demonstrating moderate to large effects of resistance training interventions on muscle strength and functional outcomes in ADT patients [24, 25]. This analysis determines that 44 participants (22 per group) provide adequate statistical power to detect the hypothesized interaction effect for the primary outcome measures. Accounting for an anticipated 15% dropout rate, based on previous reports from supervised exercise interventions in cancer survivors, 52 participants are targeted for recruitment (26 per group randomized to either the supervised velocity-based training program or the home-based control intervention).

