Physical exercise has emerged as a promising strategy for reducing the side effects of ADT, supported by several systematic reviews and meta-analyses [11, 12]. Studies have demonstrated that structured exercise programs can preserve muscle mass, protect bone density, decrease fatigue, and enhance psychological well-being in this population. Nevertheless, despite the expanding evidence base, a crucial gap exists in standardized, evidence-based exercise guidelines specifically developed for this population. Although generic exercise recommendations are available for cancer patients [13], the distinct physiological and psychological sequelae experienced by men receiving ADT require more targeted interventions. Current literature demonstrates significant heterogeneity in exercise prescription parameters (e.g., supervised versus unsupervised, frequency, progression strategies), creating challenges for clinicians seeking to implement evidence-based practice [14].

The development of standardized exercise programs for specific clinical populations requires careful consideration of multiple factors, including baseline functional status, treatment-related limitations, and progression parameters [15]. Exercise programs for men receiving ADT must address both the physiological deconditioning and psychological impact of treatment while ensuring safety and feasibility. Previous protocols have demonstrated varied success, yet most lack the specificity and rigorous evaluation methods required for widespread clinical implementation [16]. Of particular importance are considerations regarding the timing of exercise initiation relative to ADT commencement, the balance between resistance and aerobic training components, and strategies for incorporating behavioral support interventions to enhance adherence [17].

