### Participants

#### Eligibility criteria

Male individuals of legal age diagnosed with locally advanced or metastatic prostate cancer and undergoing androgen deprivation therapy (ADT) are eligible for inclusion in this randomized controlled trial. The primary objective was to assess the impact of a structured physical exercise intervention on physical function, cancer-related fatigue, and quality of life in this patient population. Participants are randomly allocated to one of two groups: those in the intervention arm received supervised exercise in accordance with the SPoRT-PCa-ADT Program, while those in the control arm are provided with a home-based exercise regimen following an initial evaluation, supported by weekly telephone follow-ups.

The inclusion and exclusion criteria are presented in the Table 1, following the recommendations of previous randomized controlled trials to target an clinically homogeneous population, maximizing potential benefits and be consistent with exercise guidelines for cancer patients [8, 22].

**Table 1 Tab1:** Inclusion and exclusion criteria

Inclusion criteria	Male participants aged 18–80 years Diagnosis of locally advanced or metastatic prostate cancer Currently receiving androgen deprivation therapy (ADT) Treatment at Urology and oncology departments within the University Clinical Hospital “Virgen de la Arrixaca” healthcare network Legal capacity and signed informed consent Ability to attend supervised sessions or perform home-based exercises safely Physician clearance for exercise participation
*Exclusion criteria*	Unwillingness to participate in the study Inability to complete adequate follow-up Uncontrolled or symptomatic metastatic bone disease Physical disabilities that would prevent participants from safely completing the protocol Severe cardiovascular disease or contraindications to exercise determined by assessment Participation in structured resistance training within the previous 6 months Cognitive impairment limiting ability to follow exercise instructions Uncontrolled hypertension (> 160/100 mmHg) Active treatment for other primary cancers

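### The d = 0.5 behind the 95% power claim is justified only by strength and functional outcomes, while the primary objective also covers fatigue and quality of life

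*Protocol article*

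**What the plan says.** Three statements in the protocol article bear on this point.

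- **Primary objective (Eligibility criteria).** The trial is to assess the "impact of a structured physical exercise intervention on physical function, cancer-related fatigue, and quality of life in this patient population". No separate list of primary outcomes is given, and no single primary endpoint is named.
- **Source of the effect (Sample size).** The calculation uses "effect size f = 0.25 (converted from Cohen’s d = 0.5"), with "α error probability = 0.05" and "power (1-β error probability) = 0.95". The value of d is attributed to earlier reports of "moderate to large effects of resistance training interventions on muscle strength and functional outcomes in ADT patients".
- **Scope of the claim (Sample size).** The resulting 44 participants are said to "provide adequate statistical power to detect the hypothesized interaction effect for the primary outcome measures". The plural carries no restriction.

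On fatigue and well-being, the Background says that exercise programmes can "preserve muscle mass, protect bone density, decrease fatigue, and enhance psychological well-being in this population". The Patient-reported outcomes section describes the BFI-SF and FACT-P as sensitive to change. Neither place gives a magnitude, an SD or a minimal important difference.

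**The concern.** The evidence cited for d covers one of the three domains in the primary objective, while the power claim reaches all the primary measures without distinction. For fatigue and quality of life the reader is given a power figure with no stated basis.

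This affects how the results are read. A non-significant difference on the BFI-SF or FACT-P, set against a published 95% power, invites the conclusion that supervision adds nothing in these domains. If the true effects there are smaller than d = 0.5, the trial could easily miss them, and the 95% figure would hide that.

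**Working it through.** **Inputs, all from Sample size:** f = 0.25 (d = 0.5, so f = d/2), α = 0.05, target power 0.95, 2 groups, m = 3 measurements, correlation ρ = 0.5, ε = 1, 15% dropout.

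**1. The plan's own figure.** For the repeated-measures within-between interaction, λ = f²·N·m·ε/(1 − ρ), with (m − 1) and (N − 2)(m − 1) degrees of freedom.

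- N = 44: λ = 0.0625 × 44 × 3 / 0.5 = 16.5, df 2 and 84, power 0.956.
- N = 42: power 0.946. So 44 is the smallest even number that reaches 0.95.
- Dropout: 44 / 0.85 = 51.8, rounded up to 52.

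Both stated figures reproduce.

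**2. Same model, changing only d.** The article gives no effect for fatigue or quality of life, so the values below 0.5 are assumptions.

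| d | Power at N = 44 | N for 95% power |
|---|---|---|
| 0.5 | 96% | 44 |
| 0.4 | 82% | 66 |
| 0.3 | 56% | 116 |
| 0.2 | 28% | 260 |

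**3. Does 95% stand for the physical outcomes, where d does have a stated source?** Two checks suggest not.

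- *Number of measurements.* The Assessment protocol section provides a week-12 assessment of patient-reported outcomes only (the Design section is not consistent with this). With m = 2, λ = 0.0625 × 44 × 2 / 0.5 = 11, df 1 and 42, power 0.90; 54 men would be needed for 95%.
- *Planned test.* The Statistical analyses section specifies ANCOVA on post-intervention values, adjusted for baseline and the two stratification factors. Take d = 0.5 as the post-intervention difference, with 22 per arm and baseline correlation r = 0.5. The residual SD is √(1 − 0.25) = 0.866, the standard error 0.866 × √(2/22) = 0.261 and the noncentrality 0.5 / 0.261 = 1.91. On 44 − 5 = 39 df, two-sided 0.05, power is 0.46. This holds for any outcome with that d and r.

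**4. What 22 per arm can detect under that ANCOVA (80% power, two-sided 0.05).** The required noncentrality is about 2.87, so the detectable d is about 2.87 × √(2/22) × √(1 − r²).

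| Baseline correlation r | Detectable difference (SD) |
|---|---|
| 0.4 | 0.79 |
| 0.5 | 0.75 |
| 0.6 | 0.69 |
| 0.7 | 0.62 |

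All these figures use an unsplit α of 0.05. The Bonferroni correction across outcomes in the Statistical analyses section would lower the powers and raise the detectable differences. With three tests (an assumed count), step 1 gives 89.5% instead of 95.6%.

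**The case against.** The strongest reply is that this is a gap in justification and not a wrong number. A medium effect is a common planning value, and the plan takes the lower end of the range it cites. The two cited sources cannot be checked here and may also report fatigue or quality of life. All of that stands: d = 0.5 could be true for the questionnaires.

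It can also be said that the primary outcomes are inferred. The article does not say that power holds for every primary outcome, and the three domains come from one sentence on the objective. Since d is justified by strength and function, perhaps only those were meant. But no narrower list appears, so the unrestricted plural reaches the questionnaires as the text is written.

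Three stronger readings are tempting, and the documents do not support them.

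- *A strength effect cannot carry over to questionnaire scores.* No passage says so. The article is silent on transfer in either direction.
- *Men with little fatigue may enrol, so there is little room to improve.* Table 1 sets no minimum fatigue, but no baseline fatigue data are given, and the Background reports that fatigue is considerable in men on ADT.
- *The 46% shows that fatigue in particular is underpowered.* That figure comes from the change of test, applies equally to strength, and says nothing about which outcome d was taken from.

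Finally, nothing in the article says that a null result will be read as no effect, and effect sizes are to be reported. The misreading is a risk that the power sentence creates, not a stated intention.

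**Conclusion.** The point holds as a mismatch between the stated source of d and the scope of the power claim. The calculation itself is correct. For fatigue and quality of life, 95% holds only if their effect is also about d = 0.5 and their correlation about 0.5, and the article supports neither for these outcomes specifically. If d were 0.4, 0.3 or 0.2, the plan's own model would give 82%, 56% or 28%.

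A reader might infer that the 95% is at least sound for strength and function and could be kept there. It is not: the same model gives 90% with two measurements, and the planned ANCOVA gives about 46% at a post-intervention d of 0.5 and r = 0.5. A rewritten sentence that kept 95% for the physical outcomes would still be unsupported.

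**What to change.** In Sample size:

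1. Withdraw the unrestricted 95% power claim, and say that d = 0.5 rests on strength and functional evidence only. Do not keep 95% for those outcomes.
2. For the BFI-SF, the FACT-P and the physical outcomes, state the difference that 22 men per arm can detect with 80% power under the planned ANCOVA: about 0.75 SD at a baseline correlation of 0.5 (0.79 at 0.4, 0.62 at 0.7). Convert it to scale points where an SD is available, and say whether α is split across outcomes.
3. In Statistical analyses, commit to reporting adjusted differences with 95% confidence intervals. State that a non-significant fatigue or quality-of-life result will not be read as no effect on the strength of the 95% figure.

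The cost is wording only, with no extra participants, visits or assessments. The downside is a less favourable power statement.

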**Methods/design:**

This randomized controlled trial with two parallel arms compares a 24-week supervised progressive resistance training program (SPoRT-PCa-ADT) with a control group receiving personalized home-based training following initial assessment and weekly telephone follow-up. The SPoRT-PCa-ADT Program utilizes velocity-based training methodology, progressing through three distinct phases (adaptation, development, maintenance) with intensity corresponding to 60% 1RM (mean propulsive velocity 0.92 m/s) and a 10% velocity loss threshold. The exercise protocol focuses primarily on squat movement patterns with real-time velocity feedback and incorporates daily readiness assessment to accommodate treatment-related fatigue fluctuations. Control group participants receive structured written instructions for home-based resistance training including warm-up and three effective sets of 12 repetitions of box squats, to be performed two to three times per week on non-consecutive days, with weekly telephone monitoring. The comprehensive assessment protocol includes progressive loading tests, vertical jump assessment, isometric strength measurement, and patient-reported outcomes measuring fatigue, quality of life, psychological distress, urinary function, and sleep quality. Assessments occur at baseline, midpoint (patient-reported outcomes only), and post-intervention, with additional biomarker collection.

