### Assessment protocol

All participants undergo identical assessment procedures irrespective of group allocation. Baseline assessments are conducted within two weeks prior to randomization, and post-intervention assessments are scheduled within two weeks following completion of the 24-week intervention period. Midpoint assessments of patient-reported outcomes are conducted at week 12 and are administered either at the training center or during specialized urological consultations as part of routine oncological follow-up. To reduce the influence of diurnal variation, all physical performance assessments are scheduled at the same time of day for each participant (± 1 h). Participants are instructed to refrain from strenuous physical activity for 48 h prior to testing, maintain adequate hydration, and abstain from caffeine and alcohol for 24 h before each assessment (Fig. 2).

Physical assessments are conducted by qualified sports scientists with training in exercise oncology. Due to logistical constraints, assessors are not blinded to group allocation. However, patient-reported outcomes are collected using standardized, self-administered questionnaires to mitigate potential assessor bias. Venous blood samples are drawn by certified phlebotomists and analyzed by laboratory technicians blinded to group assignment. To ensure procedural consistency, comprehensive standard operating procedures (SOPs) are developed prior to study initiation, and all research personnel complete structured training. Ongoing quality control procedures are implemented throughout the study to uphold methodological rigor.

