### Statistical analyses

Statistical analyses will be performed using JAMOVI (version 2.5, The JAMOVI Project, Sydney, Australia). Descriptive statistics will be calculated for all variables, with data presented as means and standard deviations for continuous variables and frequencies and percentages for categorical variables. Graphical representations will be generated using GraphPad Prism (version 10, GraphPad Software Inc., San Diego, CA, USA).

The primary analysis will include all participants who completed both baseline and post-intervention assessments in their respective groups. Additional sensitivity analyses will be conducted using intention-to-treat principles, with missing data handled using multiple imputation by chained equations (MICE) with predictive mean matching for continuous variables. For all outcome measures, analysis of covariance (ANCOVA) will be used to compare post-intervention values between groups while adjusting for baseline values and stratification variables (age group and ADT duration).

Bonferroni post-hoc corrections will be applied for multiple comparisons across outcome measures. Effect sizes will be calculated using Cohen’s d for between-group differences and partial eta-squared for ANCOVA models, with values of 0.2, 0.5, and 0.8 considered small, medium, and large effects for Cohen’s d, respectively [45]. For all analyses, *p* < 0.05 will be considered statistically significant. Per-protocol analyses will be conducted as sensitivity analyses, including only participants with ≥ 85% adherence. Exploratory subgroup analyses will examine potential effect modification by baseline characteristics including age, ADT duration, and baseline functional status. Correlation analyses will examine relationships between changes in objective physical performance measures and patient-reported outcomes within each group.

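### The 95% power claimed for 44 participants is for a different test and a mis-converted effect size; the planned ANCOVA has about 46% power for d = 0.5 at the protocol's own correlation of 0.5

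*Protocol article*

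**What the plan says.** The Sample size section names the time by treatment interaction as the primary analysis. The test is "an F-test for ANOVA: repeated measures, within-between interaction is selected", with "effect size f = 0.25 (converted from Cohen’s d = 0.5", "α error probability = 0.05", power 0.95, two groups, "number of measurements = 3 (baseline, midpoint, post-intervention", correlation 0.5 among repeated measures and sphericity. It concludes: "This analysis determines that 44 participants (22 per group) provide adequate statistical power to detect the hypothesized interaction effect for the primary outcome measures". With 15% dropout, the recruitment target becomes 52. The choice of d is supported by earlier findings on strength and function after resistance training in men on ADT.

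The Statistical analyses section plans no interaction test. For all outcomes, "analysis of covariance (ANCOVA) will be used to compare post-intervention values between groups", adjusted for baseline, age group and ADT duration, in participants with both a baseline and a post-intervention assessment. It adds a Bonferroni correction across outcomes.

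On the schedule, the abstract says: "Assessments occur at baseline, midpoint (patient-reported outcomes only), and post-intervention". The Assessment protocol section agrees: "Midpoint assessments of patient-reported outcomes are conducted at week 12". The Design section reads as though physical outcomes were also assessed at week 12.

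**The concern.** Three features of the calculation do not fit the trial.

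1. **Test.** The sample size belongs to an interaction test that the analysis section does not contain.
2. **Visits.** Three measurements are counted. By the abstract and the Assessment protocol section, the squat, jump and isometric tests are done only twice, and d is justified on strength and function. The week-12 questionnaires do not enter the ANCOVA either.
3. **Effect size.** f = d/2 describes two groups compared at one time. It is not the interaction f produced by a difference of d at the end of the study.

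The justification for d also refers to resistance training in general. Both arms here do squat-based resistance training, and the protocol gives no reason why supervised and home training should differ by 0.5 SD.

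The power statement is the trial's case for its size. If power for the stated effect is below one half, the trial is more likely to miss that effect than to find it. Readers who trust the 95% could then take a null result as evidence that supervised and home training do equally well.

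**Working it through.** **Inputs from the Sample size section:** d = 0.5, f = 0.25, alpha 0.05 (taken as two-sided), correlation ρ = 0.5, m = 3 measurements, N = 44 evaluable, 15% dropout. **From the Statistical analyses section:** ANCOVA with three covariates (baseline and two strata). **Assumptions:** d is in SD units of the post-intervention value, the SD is the same at each visit, and 0.5 is also the correlation between baseline and week 24.

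**1. The plan's own figure.** For the within-between interaction with k = 2 groups, λ = f²·N·m/(1−ρ), df1 = m−1 and df2 = (N−2)(m−1).
- N = 44, m = 3: λ = 0.0625 × 44 × 3/0.5 = 16.5, df 2 and 84, power 0.956.
- N = 42: power 0.946. So 44 is the smallest even total that reaches 0.95.
- Dropout: 44/0.85 = 51.8, rounded up to 52.

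Both stated numbers reproduce.

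**2. Visit count alone.** With m = 2 and f = 0.25: λ = 0.0625 × 44 × 2/0.5 = 11.0, df 1 and 42, power 0.900. Reaching 0.95 takes N = 54.

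**3. Effect-size conversion.** Let δ_t be the group difference in SD units at visit t. The interaction effect is f = √(mean over t of [(δ_t − mean δ)/2]²). Randomisation gives δ = 0 at baseline in expectation.

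| Difference by visit | f | Power at N = 44 |
|---|---|---|
| 0, 0.5 (two visits) | 0.125 | 0.37 |
| 0, 0.25, 0.5 (linear) | 0.102 | 0.29 |
| 0, 0.5, 0.5 (full by midpoint) | 0.118 | 0.37 |

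For two visits the deviations are ±0.25, half of which is 0.125. In reverse, f = 0.25 means a final difference of 1.0 SD (two visits), 1.06 SD (three visits, full effect by midpoint) or 1.22 SD (three visits, linear).

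**4. The planned ANCOVA.** Noncentrality = d/√(1−ρ²) × √(n/2), with n = 22 per arm and 44 − 5 = 39 df.
- 0.5/√0.75 × √11 = 0.577 × 3.317 = 1.91, against a critical t of 2.02. Power is 0.463.
- A simulation of the full model gives 0.44. It is slightly lower because it includes chance imbalance in the covariates.
- With all 52 completing, power is 0.53.

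| Baseline to week-24 correlation | Power, N = 44, d = 0.5 |
|---|---|
| 0.3 | 0.40 |
| 0.5 | 0.46 |
| 0.7 | 0.62 |
| 0.8 | 0.77 |
| 0.9 | 0.96 |

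**5. What 44 completers can detect (ρ = 0.5).** d = 0.75 with 80% power (noncentrality 2.87) and d = 0.97 with 95% power (3.71). For d = 0.5, 49 per arm are needed for 80% and 79 per arm for 95%.

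**6. Multiplicity.** All of the above uses alpha 0.05. As an illustration, dividing alpha by three lowers the ANCOVA power for d = 0.5 to 0.29.

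**The case against.** The strongest reply is that two of the three mismatches do little harm. ANCOVA adjusted for baseline is at least as efficient as a two-visit interaction test. At the week-24 difference that f = 0.25 really implies, the planned ANCOVA with 22 per arm has power 0.96 (d = 1.0) to 0.995 (d = 1.22). So neither the change of test nor the visit count brings power below the stated 95%; the conversion of d to f accounts for the fall. This is right, and it identifies the error that matters most. It does not rescue the claim, because the protocol states its target as d = 0.5.

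The visit count is also less clear-cut than the other points. The stated objective covers physical function, fatigue and quality of life, and the last two are questionnaire outcomes with three assessments. The Design section appears to place physical tests at week 12 as well. What stands is that the document disagrees with itself about week 12, and that the ANCOVA uses two time points in any case.

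The 46% depends on treating the stated 0.5 as the correlation between baseline and week 24, and on d being in post-intervention SD units. The protocol confirms neither, which is why a range is shown. Power of 95% would need a correlation of about 0.9.

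Two smaller points also stand. The comparators in the studies cited for d cannot be checked here, so it is fair to say only that the protocol does not justify d for supervised versus home training. And the plan announces no equivalence conclusion, so misreading a null result is a risk, not something the plan does.

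**Conclusion.** The concern holds. The software arithmetic is correct, but the inputs do not describe this trial's effect or its analysis. For the stated d = 0.5 and 44 completers, power is about 46% with the planned ANCOVA at correlation 0.5, and between 40% and 62% for correlations from 0.3 to 0.7. Keeping the interaction test instead would give 29% to 37%, so bringing the two sections into line would not restore 95%. The wrong conversion of d to f is the main cause. The visit count is minor (95.6% to 90.0%), and the test mismatch means that the published calculation is not about the analysis that will be run. These figures assume 15% dropout, equal SDs across visits and no multiplicity correction; the planned Bonferroni correction would lower them. The power statement has to be corrected before it is relied on.

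**What to change.** Replace the Sample size calculation with one for the ANCOVA: baseline and week 24, a stated baseline to week-24 correlation (0.5, with a range), two-sided alpha 0.05, and one named primary outcome. Remove the three-measurement input and the f = 0.25 conversion. State that d is the difference between supervised and home training, in post-intervention SD units.

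If 52 are still randomised, report what the 44 expected completers deliver at correlation 0.5: about 46% power for d = 0.5, 80% for d of about 0.75 and 95% for d of about 0.97. If more than one outcome shares alpha, repeat the figures at the corrected level. Reconcile the Design section with the Assessment protocol section on what is measured at week 12.

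This costs one paragraph and the matching registry text. It needs no extra participants, but the stated power becomes much less favourable. If the sponsor wants to keep d = 0.5 as the target, the alternative is a larger trial: 98 completers for 80% power (98/0.85, so 116 randomised) or 158 for 95% (158/0.85, so 186 randomised).
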